## Background

Pain is one of the most common complications for patients undergoing surgery. According to previous studies, almost 80% of patients undergoing spinal surgery suffer from acute postoperative pain [1], and over 60% of these patients might have persistent postoperative pain [2]. Poor perioperative pain management was an independent risk factor for persistent postoperative pain [3] and could increase the risk by 3 times [4]. Elderly patients with postoperative pain might have impaired cognitive function [5], which increases the risk of senile dementia [6]. Severe postoperative pain could also influence the emotional and mental health of patients [7, 8], which could be associated with unfavorable prognoses for the patients. Moreover, inadequate acute postsurgical pain management could result in longer hospitalization, decreased satisfaction, and higher hospital costs. Therefore, effective perioperative pain management, especially appropriate management of acute postoperative pain, is one of the most important links to help enhance the recovery of surgical patients.

One of the most challenging issues during the perioperative period is providing appropriate pain control measures to enhance the recovery of patients. Over the last decade, opioids have been the most commonly used drug in perioperative pain management strategies. However, the administration of opioids could be compounded by aspects of misuse, overdose, and addiction. Furthermore, clinical adverse events such as nausea and vomiting and respiratory depression have limited the use of opioids. In 2016, the American Society of Anesthesiologists (ASA) and American Society of Regional Anesthesia and Pain Medicine (ASRAPM) jointly published consensus guidelines for acute pain management. These guidelines indicate that ketamine [9] and pregabalin [10] can be used for the treatment of postsurgical pain.

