The mechanisms underlying postsurgical pain might be peripheral and central sensitization because of nerve injury and inflammatory responses at the operative site. Previously, researchers have suggested that central pain sensitization might be related to N-methyl-d-aspartate (NMDA) receptor activation [11]. Ketamine, an NMDA receptor antagonist, reduces central pain sensitization by blocking the activity of NMDA receptors. A related meta-analysis found that intravenous ketamine could reduce VAS scores in the 24~48-h postoperative period and decrease opioid consumption [12]. S-Ketamine, one of the enantiomers of ketamine, is a more effective analgesic and has fewer side effects than ketamine. Regarding the effects of S-ketamine on acute postsurgical pain, a meta-analysis of 12 randomized controlled trials showed that intravenous S-ketamine could decrease the intensity of pain and opioid requirements only 24 h after surgery and may increase the incidence of psychotomimetic adverse events [13]. Unfortunately, the evidence level was only moderate or even low. Due to the differences in the S-ketamine intervention protocols and the types of surgery, more high-quality studies are needed.

At the same time, gabapentinoids (gabapentin and pregabalin) have gained more attention from researchers for their significant effect on neuralgia. These compounds can inhibit the modulation of neuronal excitability by blocking α2–δ subunits of presynaptic, voltage-dependent calcium channels, which are upregulated in central sensitization processes [11]. A meta-analysis of preoperative gabapentinoids for acute postoperative pain reported that gabapentinoids were associated with reduced pain scores and cumulative morphine consumption during the 48-h postoperative period [1]. In the same year, another meta-analysis showed the effectiveness of preoperative pregabalin on acute postsurgical pain [14]. In contrast, in 2020, a meta-analysis including 281 trials investigated the effect of perioperative gabapentinoids on postoperative acute pain and reported the noneffective analgesic effects of gabapentinoids in adult patients during the postoperative period [15].

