### Perioperative anesthesia management

Perioperative anesthesia management will be standardized. After entering the operating room, the patients will be given standard electrocardiography monitoring. Anesthesia will be induced with propofol, sufentanil, and rocuronium/cisatracurium. Total intravenous anesthesia depends on target-controlled infusions and will be chosen to maintain anesthesia with propofol and sufentanil and keep the bispectral index between 40 and 60. Remifentanil will be prohibited in this study. For the potential impact on the evaluation of the operation, nerve block will not be considered. In addition, local wound infiltration (0.5% ropivacaine 20 ml) will be permitted before skin suturing if required by the surgeon. All the participants will be given the usual postoperative analgesia therapy by postoperative patient-controlled intravenous analgesia (PCIA, 0.5 ml per bolus (containing 0.5 μg sufentanil) with a lockout period of 15 min, 100 ml total), which will include 100 μg sufentanil and 16 mg ondansetron during the 2-day postoperative period. In the ward, all patients will receive parecoxib sodium (40 mg IV BID) or flurbiprofen axetil (50 mg IV BID) to receive the standard postoperative analgesic for at least 3 days. If the patients are experiencing moderate or severe pain (VAS score ≥ 40 mm), rescue analgesia will be given, including 0.5 μg sufentanil IV in the postanesthesia care unit (PACU) or 1 tablet Tylox (contained 325 mg acetaminophen and 5 mg oxycodone per tablet) in the ward. If the pain persists, the patients will receive 1 dose of 50 to 100 mg of intramuscular tramadol. All analgesic doses and names will be clearly recorded.

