**Fig. 2 Fig2:**
[figure not shown]
Standard Protocol Items: Recommendations for Interventional Trials (SPIRIT) figure showing the schedule of enrollment, intervention, and assessments

Secondary outcomes include the following:Acute pain assessment: the maximal VAS score (when the patients felt the most intense pain over the last 24 h before being interviewed) 0–2 h, 2–24 h, 24–48 h, 48–72 h after leaving the operating room and 24 h before discharge; the incidence of acute moderate-to-severe postsurgical pain at each other time point (defined as the VAS score ≥ 40 mm)Subacute or chronic pain assessment: The incidence of postsurgical pain was assessed by a number rating scale (NRS: 0~10) at 1 month and 3 months (defined as an NRS score > 3)Neuropathic pain assessment: the short-form McGill pain questionnaire-2 (SF-MPQ-2) scores at 1 month and 3 months postoperativelyTotal opioid consumption within the 48 h period after surgeryEffective or noneffective button presses for PCIAQuality of anesthesia emergence evaluated by a 15-item quality of recovery scale (QoR-15) on POD3 and at dischargeThe incidence of psychotic side effects (such as hallucinations and dissociative symptoms) was determined using the Brief Psychiatric Rating Scale (BPRS) and Clinician-Administered Dissociative States Scale (CADSS) at 2 h after surgery, POD1, POD2, and POD3Adverse events included drug-related (palpitation, hypertension, dizziness, diplopia) and operation- or anesthesia-related complications, the incidence of PONV, and the incidence of postsurgical delirium at 2 h after surgery, POD1, POD2, and POD3Other outcomes: perioperative depressive/anxious symptoms assessed by the Patient Health Questionnaire 9 (PHQ-9) and Generalized Anxiety Disorder scale (GAD-7) on POD3, at discharge, and 1 month and 3 months after surgery

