#### Adverse event reporting and harms

The follow-up investigators will pay close attention to the subjects during the intervention. If any adverse events (AEs) occur, the responsible investigator will report to the principal researcher immediately. If AEs are common and the patients’ symptoms are mild, we will supply thorough symptomatic support and treatments with close monitoring. If AEs become severe, the intervention will be stopped at once, professional doctors from various fields to immediately help the patients. Based on the relationships between AEs or serious adverse events (SAEs) and the drugs being assessed in this study, the project management team will consider whether unblinded allocated interventions are needed. If the AEs are so serious that they might impact regular clinical treatment and threaten patient safety, the research team will perform the emergency unblinding process and report the interventions to the surgeon in charge of the subjects at once. All AEs will be followed up until resolution. All adverse events will be documented in the final written report of this study and will be reported to the Institutional Review Board by the principal investigator.

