The primary concern is the potential inadequate analgesia in the control group after the surgery. The PCIA device is not a regular part of the therapeutic regimen during the postoperative period in this study hospital. As a result, we designed a usual PCIA procedure for all the participants to ensure basic postoperative analgesic treatment. If the participants experienced a moderate or severe level of pain, rescue analgesia was administered. The secondary concern is in regard to active placebo for the preoperative pregabalin capsule. In 2017, Hah’s team designed a randomized clinical trial to evaluate the effects of perioperative gabapentin on pain resolution in a mixed surgical population [17]. The researchers considered the sedating effects of preoperative gabapentin, so they chose lorazepam as the preoperative active placebo. Sleepiness is one of the common side effects of this kind of drug. However, in our pilot study, we did not observe obvious sleepiness in the participants before the surgery after taking pregabalin, and we will administer an injection of midazolam as a standard step after the patients enter the operating room; therefore, our research team decided to use the starch capsule as the placebo capsule at all time points. Furthermore, we chose total intravenous anesthesia as the standard maintenance of anesthesia with propofol and sufentanil, and propofol injection depended on target-controlled infusion (TCI). Our anesthesia management protocols might be different from those of previous studies. However, total intravenous anesthesia dependent on TCI technology can be more convenient to calculate and analyze possible drug interactions after the completion of the study. Moreover, we did not previously find any adverse events during the pilot study that are of concern, such as intraoperative awareness or delayed recovery.

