The choice of the dosages of these two trial drugs was deliberate. Based on a related meta-analysis [3], intravenous ketamine does not increase complications related to the central nervous system (such as delirium and hallucinations). A meta-analysis [18] on the effect of pregabalin on chronic pain suggested that doses as high as 300~600 mg pregabalin per day do not increase the incidence of severe adverse events. Moreover, the guidelines on pain management [10] have suggested the following recommended dosages of these two drugs: a 0.5-mg/kg bolus of ketamine with a continuous intravenous infusion dose of 0.12 mg/kg h (2 μg/kg min) and a maximum continuous infusion dose that does not go over 10 μg/kg min; a 150~300-mg preoperative dose of pregabalin and a postoperative dose of 150~300 mg per day. Based on the above information, these two trial drugs in our study will be used at lower dosages. The purpose of this dose design is to keep the participants as safe as possible while relieving postsurgical pain.

In conclusion, this study is a randomized controlled trial to explore a better method to treat postsurgical pain. The expected outcome is that perioperative esketamine combined with pregabalin can safely and effectively relieve postsurgical pain, and the results of this study can expand the understanding of perioperative pain management.

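### The named drug-related adverse events leave out sleepiness, which the protocol itself calls common for the pregabalin class, so postoperative sedation has no scheduled assessment in either arm

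*Protocol article*

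**What the plan says.** The secondary outcomes (Protocol article, Outcomes, after the Fig. 2 caption) name the adverse events as "drug-related (palpitation, hypertension, dizziness, diplopia) and operation- or anesthesia-related complications". They add nausea and vomiting and delirium, checked at 2 h, POD1, POD2 and POD3. Psychotic side effects are a separate item, rated on two named scales at the same four times. Sedation or sleepiness is not named as an outcome anywhere in the article.

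The Discussion, when explaining why an inert rather than a sedating placebo was chosen, says of gabapentinoids: "Sleepiness is one of the common side effects of this kind of drug". It sets this aside because "in our pilot study, we did not observe obvious sleepiness in the participants before the surgery after taking pregabalin", and because midazolam is given routinely once the patient is in the operating room.

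The Intervention section gives the combined arm pregabalin before surgery and until POD 14, and esketamine from after induction through 48 h postoperatively. Both arms also have a patient-controlled pump, "which will include 100 μg sufentanil and 16 mg ondansetron during the 2-day postoperative period".

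On general reporting, Adverse event reporting and harms states: "All adverse events will be documented in the final written report of this study". The Abstract says that safety will be examined, and the Discussion expects to find that "perioperative esketamine combined with pregabalin can safely and effectively relieve postsurgical pain".

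**The concern.** The article states a list of drug-related events and leaves out a harm that it attributes to one of its own trial drugs. The list is closed as printed: four events in brackets, with no wording to mark them as examples, whereas the psychotic side-effect item is worded as open.

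An event that is looked for in every patient at fixed times gives a rate with a known denominator. An event that enters the record only when someone judges it worth reporting gives a count that depends on that judgement. Postoperative sleepiness is easily taken as ordinary recovery and left unrecorded. An absence of reports would then not be an absence of sedation, and no later analysis can recover what was not recorded. The safety statement at the end of the trial would be weakest on a side effect that the protocol had itself foreseen.

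**Working it through.** The point rests on no figure in the plan, so the check is a comparison of sections, followed by a short calculation to show what the fix can and cannot deliver.

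**1. Harms named in the article against harms with a named assessment**

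| Harm | Where the article names it | Attributed to | Named assessment |
|---|---|---|---|
| Psychotomimetic events | Background ("may increase the incidence of psychotomimetic adverse events") | S-ketamine | Yes, two scales at four times |
| Nausea and vomiting | Background ("clinical adverse events such as nausea and vomiting and respiratory depression have limited the use of opioids") | Opioids | Yes, at four times |
| Respiratory depression | Background (same sentence) | Opioids | Not named; could fall under anesthesia-related complications |
| Sleepiness | Discussion ("Sleepiness is one of the common side effects of this kind of drug") | Pregabalin class | None |

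Sleepiness is the only harm in this table that is attributed to a trial drug and has no named assessment.

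**2. Does the stated reason cover the exposure?** The pilot observation on sleepiness and the midazolam step both concern the time before surgery, and both serve the choice of placebo capsule. The same paragraph also reports that the pilot raised no worrying adverse events, giving slow recovery from anesthesia as one example. That bears on emergence, but not on the two days of infusion and pump opioid or on the further days of capsules. The postoperative exposure is therefore largely uncovered.

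**3. What unscheduled reporting does to a rate.** Let p be the true proportion of patients with sleepiness and c the unknown share of cases that reach the record. The expected recorded rate is c × p. If c is the same in both arms, which blinding supports, the recorded difference is c × (p₁ − p₀). It is shrunk towards zero by a factor that nobody can estimate. With a scheduled check, c is close to 1 by design.

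**4. What a scheduled check would deliver.** Inputs from Sample size calculation: 90 patients at 1:1, so 45 per arm; with 20% withdrawal, 45 × 0.8 = 36 per arm.

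- Upper one-sided 95% limit after zero events, 1 − 0.05^(1/n): n = 45 gives 6.4%; n = 36 gives 8.0%. These limits come from the sample size and apply to every listed event. They do not measure this gap. They also presuppose c = 1; otherwise the limit applies to c × p.
- Power, two-sided 5%, pooled normal approximation. The article gives no sleepiness rates, so these are assumptions:

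| Assumed rates | 45 per arm | 36 per arm |
|---|---|---|
| 10% vs 20% | 26% | 22% |
| 10% vs 30% | 67% | 57% |

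- Precision at 10% vs 20% with 45 per arm: standard error √((0.1 × 0.9 + 0.2 × 0.8)/45) = 0.0745, so the 95% interval is 10 points ± 1.96 × 7.45 = ± 14.6 points.

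Scheduling the assessment makes the rates comparable and honestly imprecise. It does not make them conclusive.

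**The case against.** The strongest reply is that sedation is already collected. The harms section covers every adverse event, mild ones included, and has follow-up investigators watching patients closely. The section on the data monitoring committee adds careful monitoring in hospital, with two anesthesiologists and a spinal neurosurgeon responsible for safety. This stands against any claim that only severe or volunteered events would be caught. Because assessors are blinded, nothing in the text makes capture unequal between arms either. What remains is that no question, definition or time is set for sedation, so sensitivity is unknown in both arms.

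A second reply is that the article condenses a fuller protocol, and that the Fig. 2 schedule and the case report forms are not shown. That is fair: a sedation item may exist there. But the article chose to print its event list, and the list as printed does not match its own Discussion.

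Stronger readings are tempting, and the document does not support them:

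- A reader might infer that respiratory depression has been overlooked as a trial-drug risk. The Background attributes it to opioids, which both arms receive, and the open category of operation- or anesthesia-related complications could hold it. The article nowhere attributes an added respiratory effect to pregabalin or esketamine.
- A reader might infer that the most expected risk goes untested. The article does not rank risks, and it does seek psychotic effects, delirium, dizziness, and nausea and vomiting.
- A reader might infer that sedation explains away lower pain scores or fewer pump presses. Nothing in the article supports this. The secondary VAS asks for the worst pain over the preceding 24 h, and a sedation score would not by itself separate the two effects.

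**Conclusion.** The point holds as a gap in ascertainment. The named drug-related events omit sleepiness, which the article calls common for the class; the reason for discounting it is preoperative; and general reporting does not give a dependable rate by arm. The consequence is a weaker basis for the safety conclusion. It is not an untested one, and the primary outcome is unaffected as far as the document shows.

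The size cannot be put as a number, because the article gives neither a sleepiness rate nor a capture rate. The power figures above rest on assumed rates and serve only to limit what the fix may promise. The verdict also assumes that Fig. 2 and the case report forms hold no sedation item. If they do, only the printed list needs correcting.

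**What to change.** Add sleepiness or sedation, graded on a named ordinal sedation score, to the listed drug-related events. Record it for every patient in both arms at the existing 2 h, POD1, POD2 and POD3 checks. Report it by arm, with the difference and its 95% confidence interval, as a descriptive safety result.

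Respiratory depression can be listed explicitly under the existing anesthesia-related complications, with a definition stated in advance and based on routine bedside observations. This is a smaller clarification.

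The cost is a few form fields at visits already planned, with no new visits, patients or change to treatment. The downside is slightly more data entry and possibly a less favorable safety profile.

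The article dates the end of recruitment at 31 August 2022. If the in-hospital checks are already complete, report sedation as unscheduled adverse event data, say so, and limit the safety statement to the events that were assessed systematically.

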### Data management

All the clinical information will be recorded in the unified case report forms designed specifically for this project and other paper documents, including informed consent forms and the protocol. After the follow-up is completed, the research paper documents will be locked in a single secure office in Beijing Tiantan Hospital, and the key will be kept by only the primary investigator and trial manager. Research data will be coded with a unique trial ID number, and no personal identifiers will be contained in the research data. The trial ID number that links identifying information to study subjects will be accessible only to the study investigators. The data will be entered into an enciphered electronic database after completion of this study. Only the principal investigator will know the password of this electronic database. All of the paper materials and the electronic database will be managed by the principal investigator until the study is complete.

### Statistical analysis

Continuous data will be described as the mean with standard deviation (SD) or median with interquartile range (IQR) based on its distribution. The histogram and Kolmogorov–Smirnov tests will be used to evaluate the normality of the data distribution. Categorical variables will be summarized as counts and percentages. The primary outcome is categorical and will be analyzed by using the chi-square test or Fisher’s exact test. Regarding the secondary outcomes, based on the type of each variable, the difference between groups will be analyzed using *t* tests, Mann–Whitney *U* tests, and chi-square or Fisher’s exact tests as appropriate. We will use the modified intension-to-treat (mITT) analysis to report our results, and we will use per-protocol (PP) analysis to perform the sensitivity analysis. The methods for estimating effects and 95% CIs will be reported in our outcomes. Sensitivity analyses will be applied to determine the statistical nature of the missing data. A two-sided *P* value of 0.05 was considered statistically significant for the primary outcome. Because of the repeated measurement, the Holm–Bonferroni method will be used to adjust the *P* value for secondary outcomes. Statistical analysis will be implemented using SPSS version 23.0 software and Stata version 14.0.

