### Randomization and blinding

Patients will be randomized 1 day before surgery using blocked, stratified randomization by independent research staff to 1 of 2 treatment groups (the combined group or the control group) after study enrollment. We will randomize the patients in a 1:1 ratio in blocks of four. The randomized allocation list will be generated by using a real-time, online system on the day before surgery. The randomization results will be maintained by independent researchers who will not participate in any other work of this study to guarantee allocation blinding. The presence of moderate or severe preoperative pain will be used as a basis for the stratification of patients (evaluated by a visual analog scale, range: 0–100, with 0, no pain; 100, the worst pain; moderate or severe preoperative pain is defined by a VAS score equal to or more than 40 mm).

Allocation concealment will be achieved using study capsules and intravenous infusions with identical appearance for placebo and drugs. All the trial drugs will be provided by a medicine company (Hengrui Induction, Jiangsu, China) with no other contribution to this trial. The appearance of all trial capsules (placebo capsules containing starch and pregabalin capsules) will be the same. Esketamine will be diluted to a concentration of 0.5 mg/ml with normal saline. Colorless 50-ml syringes containing clear esketamine or placebo (normal saline) solution will be prepared in a blinded manner by an independent research assistant. The randomization code will be marked on the syringes and the drug bottles of the study capsules. Only the study investigator who assigns participants to interventions will be unblinded to the treatment assignment. All other study researchers will be blinded to the treatment assignment, including responsible anesthesiologists and the neurosurgeons in charge of the patients, the outcome assessors, data analysts, and other relevant investigators.

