### Outcomes

The assessment of outcomes will be performed by two independent researchers. The results during hospitalization will be collected by the investigators through bedside interviews. The collection of postdischarge outcomes will be performed by telephone interview.

The primary outcome was the proportion of patients with acute moderate-to-severe postsurgical pain during the 48-h postoperative period (defined as a VAS score ≥ 40 mm). The schedule of enrollment, intervention, and assessments is presented in Fig. 2.

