### Sample size calculation

According to a previous randomized controlled trial that investigated the effect of combined ketamine and pregabalin on persistent postoperative pain, the prevalence of moderate-to-severe acute postoperative pain at 24 h after surgery was 42% in the combined group and 78% in the control group [16]. Among patients with preoperative pain, the incidence of acute moderate-to-severe postsurgical pain in the population undergoing spinal surgery is nearly 80% [1]. Based on the above data and the current clinical situation, we estimate that the incidence of acute moderate-to-severe postsurgical pain will be 30% in the combined group and 60% in the control group, with a total 2-sided type I error rate of 0.05 and a 20% withdrawal rate. Ninety patients will have to be enrolled to achieve a statistical power of 80% (*P* values of 0.05).

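### Randomization is stratified by preoperative pain but the named primary test ignores the stratum: a free efficiency gain of uncertain size, not a validity error

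*Protocol article*

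**What the plan says.** **Design.** In Randomization and blinding: "Patients will be randomized 1 day before surgery using blocked, stratified randomization", and "We will randomize the patients in a 1:1 ratio in blocks of four". The single factor is stated there too: "The presence of moderate or severe preoperative pain will be used as a basis for the stratification of patients", with moderate or severe pain defined as a VAS score of at least 40. There are therefore two strata.

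**Analysis.** Under Outcomes, "The primary outcome was the proportion of patients with acute moderate-to-severe postsurgical pain during the 48-h postoperative period", a yes/no endpoint at the same VAS cut-off. Under Statistical analysis, "The primary outcome is categorical and will be analyzed by using the chi-square test" or Fisher's exact test. The further analyses named are a per-protocol sensitivity analysis and sensitivity analyses for missing data. The stratum appears in none of them. The section promises effect estimates with 95% CIs but fixes no method for them.

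**Figures bearing on prognosis.** Sample size calculation assumes the event rate "will be 30% in the combined group and 60% in the control group". It also reports: "Among patients with preoperative pain, the incidence of acute moderate-to-severe postsurgical pain in the population undergoing spinal surgery is nearly 80" per cent. No event rate is given for patients without preoperative pain, and no expected share of patients in each stratum.

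**The concern.** Blocking within strata keeps the arms nearly balanced on preoperative pain. Chance imbalance on that factor therefore contributes almost nothing to the real variability of the treatment difference. The ordinary chi-square variance still includes that component. When the factor predicts the outcome, the standard error is larger than the design warrants, the true type I error falls below the nominal 5%, and some real effects are missed.

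What is at stake is power in a small trial. The protocol pays for balance at randomization and then does not use it in the one test that decides the result.

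**Working it through.** **Inputs from the protocol article.** Two strata, blocks of four, 1:1; 60% versus 30%; two-sided alpha 0.05; 20% withdrawal; 90 enrolled; 80% power.

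**Inputs assumed.** The share *w* of patients in the pain stratum; the control event rate in that stratum (80%, taken from the Sample size calculation section); a common odds ratio for treatment across strata.

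**1. The plan's own figure.** With the pooled-variance formula, n per arm = [1.96·√(2·0.45·0.55) + 0.8416·√(0.6·0.4 + 0.3·0.7)]² / 0.3² = (1.379 + 0.565)² / 0.09 = 41.97, so 42 per arm and 84 in total. Allowing for 20% withdrawal gives 84/0.8 = 105. The stated 90 is not reproduced. That is a separate matter, but it means two sample sizes need to be looked at:

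- 90 less 20% = 72, or 36 per arm: z = (0.3·√36 − 1.379)/0.671 = 0.628, power 73.5%.
- All 90, or 45 per arm: z = (0.3·√45 − 1.379)/0.671 = 0.944, power 82.8%.

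**2. Why the plain test is conservative.** Take no treatment effect and a 60% event rate in both arms. The chi-square test uses the total variance 0.6·0.4 = 0.24. Under stratified blocking the variance that actually operates is, to a good approximation, the within-stratum part, 0.24 − *w*(1 − *w*)(0.80 − p₀)². Here p₀ = (0.60 − 0.80*w*)/(1 − *w*) is the rate without preoperative pain. The true alpha is then about 2Φ(−1.96/√ratio), where ratio is the within-stratum variance divided by 0.24.

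| *w* | p₀ | Stratum odds ratio | Ratio | Alpha, formula | Alpha, simulated chi-square |
|---|---|---|---|---|---|
| 10% | 0.578 | 2.92 | 0.981 | 4.8% | 4.9% |
| 20% | 0.550 | 3.27 | 0.958 | 4.5% | 4.5% |
| 30% | 0.514 | 3.78 | 0.929 | 4.2% | 4.2% |
| 40% | 0.467 | 4.57 | 0.889 | 3.8% | 3.8% |
| 50% | 0.400 | 6.00 | 0.833 | 3.2% | 3.2% |
| 60% | 0.300 | 9.33 | 0.750 | 2.4% | 2.4% |

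The simulated column is for 36 per arm. The CMH test stayed between 4.8% and 5.1% in the same runs.

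**3. Power, same assumptions** (60,000 simulated trials per row, permuted blocks of four within strata, chi-square without continuity correction):

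| *w* | 36 per arm: chi-square | CMH | Gain, points | 45 per arm: chi-square | CMH | Gain, points |
|---|---|---|---|---|---|---|
| 10% | 73.1% | 74.0% | 0.9 | 82.1% | 83.0% | 0.9 |
| 20% | 73.3% | 75.1% | 1.9 | 82.4% | 84.1% | 1.7 |
| 30% | 73.6% | 76.8% | 3.2 | 82.9% | 85.6% | 2.7 |
| 40% | 74.0% | 78.9% | 4.9 | 83.4% | 87.1% | 3.8 |
| 50% | 74.6% | 80.9% | 6.4 | 83.9% | 88.8% | 4.9 |
| 60% | 74.9% | 83.0% | 8.1 | 84.4% | 90.4% | 6.0 |

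Gains were taken before rounding, so some differ by 0.1 from the difference of the columns.

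**4. Power without the 80% anchor.** With the stratum odds ratio set freely, *w* from 20% to 50%, and both sample sizes:

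| Stratum odds ratio | Gain of CMH, points |
|---|---|
| 1 | about 0 |
| 2 | 0.5 to 0.9 |
| 3 | 1.5 to 2.6 |
| 4 | 2.2 to 4.0 |
| 6 | 3.5 to 6.2 |
| 10 | 4.6 to 9.1 |

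**The case against.** **The article does not show that preoperative pain is strongly prognostic.** A reader might infer this by setting the 80% for patients with preoperative pain against the 60% assumed for all controls. The comparison does not support it. The Background section cites the same source for almost 80% in spinal surgery patients generally, with no restriction to preoperative pain. The 60% is the authors' own planning value, set below both that figure and the 78% control rate from the earlier combined-therapy trial. The 80% also refers to preoperative pain without a severity threshold, whereas the stratum requires VAS ≥ 40. This objection stands: the anchored scenario is an assumption.

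**The calculation fixes its own answer.** Holding 80% in one stratum and 60% overall forces p₀ down as *w* rises, so the stratum odds ratio is imposed (3.8 to 6.0 for shares of 30% to 50%). The eligibility criteria also exclude severe chronic pain and long-term analgesic treatment, which may make the pain stratum small; at 20% or less the anchored gain is under 2 points. This stands too. A loss of several points must not be stated as a fact about this trial.

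**The planned test is still valid.** Its type I error is at or below 5%, so the stronger reading that the primary result would be biased or falsely positive has no support. Nor can one say that the planned confidence interval is too wide, because no interval method is fixed.

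**Adjusted analysis may be left to a statistical analysis plan that is not shown.** This has less force. The article does not leave the primary test open; it names one, and the one named does not match the randomization.

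**The t and Mann-Whitney tests for the VAS secondary outcomes.** The same reasoning would apply in principle, but nothing was calculated for them and the article gives no figure linking preoperative VAS to those scores.

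**Conclusion.** The mismatch between design and test is on the page and needs no assumption. Its cost does. If preoperative VAS ≥ 40 predicts the outcome, the unstratified test is conservative and loses power; if it does not, nothing is lost. With the 80% anchor and a stratum share of 30% to 50%, the loss is about 3 to 6 points at 72 evaluable patients and about 3 to 5 at 90. The wider supportable range is about 0 to 9 points, and under 1 point at a stratum odds ratio of 2.

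A reader might infer that the stratified test would close the gap between 73.5% and the stated 80% power at 72 evaluable patients. In the anchored scenarios it reaches 80% only at shares of about 50% or more, and the shortfall itself is a sample-size question that this change does not settle.

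This is a free improvement in efficiency. In every prognostic scenario examined the CMH test gained power and held alpha near 5%; at an odds ratio of 1 it cost essentially nothing.

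**What to change.** Before unblinding, replace the primary-analysis sentence with a CMH test stratified by preoperative VAS ≥ 40 (yes/no), reported with the Mantel-Haenszel risk difference and its 95% CI. Keep the unadjusted chi-square test as a supporting analysis. If a separate statistical analysis plan already specifies this, bring the protocol wording into line with it.

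Adjusting the VAS secondary outcomes for preoperative VAS is a reasonable companion change, offered without a claimed gain.

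The cost is wording only. The stratum has to be known for every patient before allocation, and no extra patients, visits or data are needed. Timing matters: a switch to the stratified test after unblinding would be post hoc.
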